## Abstract

**Background:**

American Indian (AI) young adults in urban areas have many cultural strengths but also face unique challenges. Cultural norms within their communities strongly emphasize relationships. Previous research has found that receiving occasional positive and nondemanding messages—caring text messages—can be beneficial among people experiencing suicidality.

**Objective:**

To ameliorate increasing rates of suicide and suicidality among AI young adults, we implemented a caring text message intervention designed to increase social connectedness.

**Methods:**

This 2-arm, double-blinded, randomized controlled trial is being implemented at 2 clinical sites with large AI populations. Partnering with clinics in Albuquerque, New Mexico, and Rapid City, South Dakota, we are recruiting AI adults aged 18-34 years to participate in a caring text message study. During the baseline visit, participants complete several surveys and an interview with study staff to understand their history of suicidal behavior. After completion of the baseline visit, participants are randomized to receive the intervention—approximately 30 caring text messages—or treatment as usual. The text messaging platform selected for this study allows bidirectional messaging; while there is no expectation that participants respond, they can provide feedback or seek additional resources. Participants are followed up at 6 and 12 months postbaseline. At the final 12-month follow-up visit, they complete many of the same surveys and participate in an interview to ascertain suicidality since their initial visit. The primary outcomes of interest are suicide-related behaviors—suicidal ideation, suicide planning, suicide attempt, or thoughts and actions requiring hospitalization. Secondary outcomes include social connectedness and other measures of mental health. We will use an intention-to-treat analysis with logistic and linear regression to calculate odds ratios and risk differences (95% CIs) for binary and continuous outcomes.

**Results:**

As of June 2025, the New Mexico site has finished recruitment and follow-up assessments. The South Dakota site is still enrolling participants and has conducted the first follow-up assessments. The project has been well-received by participants.

**Conclusions:**

This randomized controlled trial will evaluate whether a caring text message intervention is effective in reducing suicidality among AI young adults in urban areas. Participants have received the culturally tailored caring text messages. This trial will help establish whether caring text messages are an effective strategy for reducing suicidal behaviors and promoting feelings of connectedness among AI young adults.

**Trial Registration:**

ClinicalTrials.gov NCT03136094; http://clinicaltrials.gov/show/NCT03136094

**International Registered Report Identifier (IRRID):**

DERR1-10.2196/71344

## Introduction

### Background

American Indian (AI) communities have a rich and diverse cultural heritage that is deeply rooted in their connection to the land, their families, and their communities [1-3]. These strengths, combined with their traditional values and beliefs, have enabled them to withstand centuries of colonization, oppression, forced assimilation, and the loss of land and resources [4]. Despite these strong cultural foundations, the rate of suicide among AI youth and young adults remains disproportionately high compared to other racial and ethnic groups in the United States [5]. It is a leading cause of mortality in many AI communities, particularly among individuals aged 10-34 years, making it a major public health concern for AI people [5]. This concern is especially pronounced among urban AI young adults, for whom risk and protective factors may differ from both non-AI peers living in urban areas and rural AI peers [6,7].

As concerns around mental health, depression, and suicidality continue to grow, the integration of behavioral health services into primary care has become increasingly common. One method of integration is through an evidence-based practice, screening, brief intervention, and referral to treatment (SBIRT) [8]. In a typical SBIRT model, patients seeking care from their primary care provider are routinely screened for substance use disorders and mental health conditions such as depression and anxiety. If they screen positive, a colocated behavioral health provider renders a brief intervention and refers the patient to further treatment [8].

The interpersonal theory of suicide is particularly relevant for young, urban AI populations, as it identifies thwarted belongingness as contributing to suicidal ideation [9,10]. Interventions that increase feelings of belonging and reduce feelings of loneliness can be effective in reducing suicide risk [11]. Previous work has found that while social support was not highly correlated with suicidality among rural AI and Alaska Native (AIAN) youth, it protects against depressive symptoms and suicidality among urban AIAN youth [6]. Community connectedness is a major cultural strength among AIAN people. Increasing people’s sense of belonging and connection to their heritage and culture may be particularly effective for improving mental health outcomes and reducing the risk of suicide [12].

Given the importance of social connections in mitigating depressive symptoms and suicidal behaviors, previous studies have sought to supplement the SBIRT protocol with caring text messages [13-15]. This text message–based intervention sends participants messages of support and encouragement periodically throughout the year [11], a modern modification of earlier interventions that delivered similar styles of message through letter or postcard [16,17]. Due to the inequitable burden of suicide, unique risk factors, and limited availability of data regarding suicide prevention—including a dearth of culturally relevant interventions—we focused our efforts on AI young adults in urban areas. Community members and our academic team cocreated brief, powerful, site-specific text messages that highlight cultural strengths or impart wisdom of local adults, and combined them with an SBIRT protocol implemented at 2 clinical sites serving AIAN people. Our study assesses the program’s effectiveness in reducing depressive symptoms, suicidal ideation, and suicidal behaviors among a group of at-risk young adults.

### Objective

This study is part of a large AIAN-specific federal research program to address youth suicide, called the Collaborative Hubs to Reduce Burden of Suicide among American Indian and Alaska Native Youth, which has several aims [18]. Our double-blinded, 2-armed randomized controlled trial is designed to test the effectiveness of a 12-month intervention that combined caring text messages with SBIRT in reducing self-reported suicide ideation, attempts, and hospitalizations, and in increasing social connectedness and retention compared to treatment as usual among urban AI young adults. This paper describes the design and implementation of our randomized controlled trial, which seeks to increase resilience through social connectedness and engagement, thereby reducing suicidal ideation, attempts, and hospitalizations. We also detail the measures and procedures of the systematic economic evaluation of the SBIRT and caring text components of the intervention to determine their relative effects on the use of health care resources and quality of life.

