### Eligibility

The population of interest for this study is young AI adults at mild, moderate, or severe risk for suicide. To participate, an individual must self-identify as AI, be between 18 and 34 years of age, and understand written and spoken English. They must complete the SBIRT process with clinic staff and screen positive for elevated risk of suicide or depression, but not be in danger of imminent self-harm. In addition, the participant must have a cell phone that can receive text messages and be willing to be contacted via text message. Participants who have contraindications (ie, are hospitalized) or are cognitively impaired are not eligible.

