#### Treatment as Usual

All participants in the study, regardless of their assigned treatment group, continued to receive the standard treatment normally provided by the clinic, including mental health services, medication management, substance abuse treatment, and case management. Data about the type and frequency of clinic visits by study participants during the study enrollment period were collected by the study team from the participants’ EHR after their study completion.

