#### Caring Texts Intervention

In addition to receiving TAU, participants assigned to the caring texts intervention group also received 28-30 supportive and nondemanding text messages; examples of these messages are available in Table 1, and the complete schedule of messages is available in Multimedia Appendix 1. The number of messages sent depended on the date of enrollment, the participant’s birthday, anniversaries, holidays, and seasonal and local events. These messages were sent over 12 months, namely, daily for the first 3 days, then 6 weekly messages, 6 biweekly messages, and 6-monthly messages. Other messages include a birthday message, a holiday message (in December), a harvest message (in November), messages acknowledging an anniversary of loss and an anniversary of hope, and 4 messages for seasonal events. The study tailored messages to reflect locally appropriate holidays, events, and celebrations, and used the local language for greetings [20]. The messages were delivered through a secure online platform, LifeWIRE (LifeWIRE Group), which was compliant with HIPAA, HiTech, and FDA regulations for electronic interactions. This platform tracked all communication, preprogrammed messages, and offered the option for individualized responses to be typed and stored for record-keeping purposes.

**Table 1 table1:** Sample messages for caring text messages sent to intervention participants by site.

Timing	FNCH^a^ message (Albuquerque)	OHC^b^ message (Rapid City)
First day after enrollment (#1)	It was nice meeting and talking with you yesterday, [displayname]^c^. You showed great courage. Thanks for trusting me. -<staff name>^d^	Hello [displayname], It was nice meeting and talking with you yesterday. You showed great courage. Thanks for trusting me. -<staff name>
Weekly (#6)	Ya’at’eeh! Keshi! Guw’aadzi! No matter how you say “hello,” everyone is welcome at the FNCH Traditional Wellness Program. Please call (XXX) XXX-XXXX for more information. - <staff name>	Aŋpétu wašté [displayname]! Sending you positive vibes. Creator has good things for you. Smudging is a good way to stay in touch with the Creator. - <staff name>

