#### Treatment Retention

Retention in the SBIRT program is assessed at 12 months. It is operationalized as a 3-category indicator (full, partial, and none) defining engagement for each participant in the appropriate level of care. The appropriate level of care is determined during the initial in-person session with the SBIRT behavioral therapist before enrollment in the study and is independent of study procedures. These variables will be included in sensitivity analyses if they appear unbalanced, although randomization and the large sample size should balance the severity of suicidality and intensity of appropriate intervention services across the study conditions.

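### The economic aim promises the relative effects of SBIRT and caring texts, but only the texts are randomised, so only their increment over SBIRT and usual care has a randomised comparison

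*Protocol article*

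**What the plan says.** Two statements in the Objective section set the aims. The trial is to "test the effectiveness of a 12-month intervention that combined caring text messages with SBIRT", with treatment as usual as comparator. The article also announces an "economic evaluation of the SBIRT and caring text components of the intervention to determine their relative effects" on resource use and quality of life. Both sentences treat SBIRT as part of what is under test, and the second treats it as one of two components whose effects can be set against each other.

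The Methods describe the arms as follows.

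- Eligibility: "They must complete the SBIRT process with clinic staff and screen positive for elevated risk of suicide or depression".
- Randomization: allocation to the intervention or to treatment as usual takes place once the baseline assessment is finished, stratified by site.
- Treatment as Usual: "All participants in the study, regardless of their assigned treatment group, continued to receive the standard treatment normally provided by the clinic".
- Caring Texts Intervention: "In addition to receiving TAU, participants assigned to the caring texts intervention group also received 28-30 supportive and nondemanding text messages".
- Treatment Retention: the appropriate level of care is fixed at the first session with the SBIRT therapist, "before enrollment in the study and is independent of study procedures". The same section says: "Retention in the SBIRT program is assessed at 12 months", in three categories (full, partial, none).

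**The concern.** The Objective names a component effect that the design does not randomise. Everyone enters through SBIRT and nobody is allocated to go without it, so the two arms cannot show what SBIRT does or how its effect compares with that of the texts.

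What is at stake is the interpretation of the economic results. To deliver the aim literally, the analysts would need a comparison outside the randomisation, for example between participants who stayed engaged with SBIRT and those who did not. Engagement is not assigned, and the level of care follows from the initial clinical assessment, so such a comparison would be open to confounding by severity. Reported under the trial's stated objective, it could be read as a randomised result.

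**Working it through.** The plan gives no figure to reproduce here; the question is whether the stated aims can be estimated from the two arms.

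**Step 1: what is assigned.** Let S stand for entry to SBIRT with its level of care, and T for assignment to texts.

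| Arm | S | T | Source |
|---|---|---|---|
| Caring texts | 1 | 1 | Eligibility; Treatment Retention; Caring Texts Intervention |
| Treatment as usual | 1 | 0 | Eligibility; Treatment Retention; Treatment as Usual |

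No arm has S = 0.

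**Step 2: what can be estimated.** Write the mean of any outcome (cost, resource use, quality of life) as a + b·S + c·T.

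- Texts arm: a + b + c
- Treatment-as-usual arm: a + b
- Difference: (a + b + c) − (a + b) = c

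The SBIRT effect b cancels from the difference and otherwise appears only in the sum a + b. In matrix form the rows are (1, 1, 1) and (1, 1, 0). The rank is 2 for 3 parameters, because the SBIRT column equals the intercept. So c is estimable, while b, b + c (the combination against no SBIRT) and any contrast or ratio of b and c are not. If texts work differently in people who have been through SBIRT, a term d·S·T adds d to the texts arm only and the difference becomes c + d: the effect of texts given SBIRT. That is still the only estimable quantity.

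**Step 3: what happens after randomisation.** S above covers entry and the initial level-of-care decision only. SBIRT use can continue, since retention is measured at 12 months, and the Objective lists higher retention among the effects under test. The arms may therefore come to differ in SBIRT use. With per-participant means, the between-arm cost difference is

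incremental cost = cost of texts + (SBIRT cost in texts arm − SBIRT cost in usual-care arm) + (other care cost in texts arm − other care cost in usual-care arm).

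The first bracket need not be zero. As allocation to texts is the only randomised difference, a non-zero expected value of that bracket is a consequence of the texts. It shows how texts alter SBIRT use, and says nothing about what SBIRT does for quality of life or other resource use. It belongs in the incremental cost.

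**Step 4: a possible exception.** Under Recruitment and Retention, some patients at the New Mexico site were found through medical records and screened by study staff. That leaves open whether each had a full SBIRT contact. It happened before randomisation, so it creates no systematic SBIRT contrast between arms.

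**The case against.** The strongest reply is that this is loose wording in an introductory section. Texts combined with SBIRT against treatment as usual can be read as ordinary add-on language, and the Methods make the contrast plain. The article condenses a fuller plan, and the economic estimand and costing rules may well be set out there. Examining SBIRT use alongside the texts is also legitimate, because texts may raise SBIRT retention and so change its cost.

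Much of this stands. The Methods fix the add-on contrast clearly, so the main-objective sentence needs only tidying. SBIRT use should be analysed by arm. The reply does not rescue the economic sentence, which names two components and promises to determine their relative effects. That is a positive statement at odds with the design, and not a detail left out for brevity.

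A reader might infer three stronger points, none of which the documents support.

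- *That the arms have identical SBIRT exposure, so the incremental cost is just the cost of the texts.* Entry and the level-of-care decision are common to both arms, but later retention may differ between them.
- *That the analysis must charge SBIRT to the intervention arm alone and so inflate the incremental cost by some multiple.* Nothing proposes this. Treatment as Usual describes record data on clinic visits for study participants without restriction to one arm, an ordinary between-arm comparison is available, and no costs are given from which to derive a multiple.
- *That the trial report will credit SBIRT plus texts with the effect.* The abstract's conclusions, the Principal Findings and the closing Conclusions all attribute any benefit to the caring texts.

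**Conclusion.** The concern holds for the stated aims. The randomised comparison supports one effect, that of adding caring texts to SBIRT and usual care. It gives no estimate of an SBIRT effect, of the combination against no SBIRT, or of one component relative to the other. This is a matter of identification, so more participants would not change it, and no numerical size applies. Randomisation, outcomes, sample size and the planned between-arm analyses are unaffected.

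The conclusion rests on reading SBIRT entry and level of care as common to both arms, as Eligibility and Treatment Retention state, and on the texts being the only assigned difference, as the two treatment-group sections state. It does not assume that SBIRT use stays equal after randomisation. The change is worth making because the aim as written promises a conclusion that the trial cannot reach.

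**What to change.** In the Objective section, and in any economic analysis plan that repeats it:

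1. State the objective as caring texts added to SBIRT and usual care versus SBIRT and usual care alone.
2. State the economic aim as the between-arm incremental cost, resource use and quality of life from adding texts. Count SBIRT use in both arms, and treat any arm difference in SBIRT retention as a consequence of the texts.
3. Delete the aim of determining relative component effects. If an SBIRT analysis is kept, label it non-randomised and descriptive.

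The cost is wording only: no new data and no change to conduct. What is given up is a component claim that the design cannot support.

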## Methods

### Setting and Participants (Study Sites)

Participants are recruited from 2 partner sites: First Nations Community HealthSource (FNCH) in Albuquerque, New Mexico, and Oyate Health Center (OHC) in Rapid City, South Dakota, operated by the Great Plains Tribal Leaders’ Health Board. Both health centers are funded in part by the Indian Health Service (IHS). As a federally qualified health center, FNCH serves all patients, while OHC primarily serves tribal members eligible to receive services through IHS. Both offer a variety of services, including primary care, behavioral health, women’s health, and urgent care or same-day services.

### Eligibility

The population of interest for this study is young AI adults at mild, moderate, or severe risk for suicide. To participate, an individual must self-identify as AI, be between 18 and 34 years of age, and understand written and spoken English. They must complete the SBIRT process with clinic staff and screen positive for elevated risk of suicide or depression, but not be in danger of imminent self-harm. In addition, the participant must have a cell phone that can receive text messages and be willing to be contacted via text message. Participants who have contraindications (ie, are hospitalized) or are cognitively impaired are not eligible.

#### Recruitment and Retention (Recontact Protocols)

As part of the regular appointment process at FNCH, patients are asked to fill out the FNCH Healthy Lifestyle Questionnaire (HLQ), which includes the Columbia-Suicide Severity Rating Scale and the Patient Health Questionnaire screenings for suicide risk and depression. The HLQ is completed by newly enrolled patients at the first appointment of the calendar year and every 3 months thereafter. Trained clinic staff review and score the completed HLQ during the patient’s visit, and this information is recorded in the electronic health record (EHR) and shared with the clinical provider. Depending on the score, the provider may offer treatment and/or referral for services. Study eligibility initially hinged on scoring positive for suicide risk (low, moderate, or severe) or depression. The clinic staff or provider informs the patient about the study. Alternatively, the patient could learn about the study from a flyer posted in the clinic. If interested, the patient was connected immediately to study staff through a warm hand-off. If a patient met eligibility criteria, the site coordinator proceeded with the informed consent procedures and the baseline interview. If the patient was unable to complete baseline procedures at that time due to time constraints, the site coordinator scheduled a time within a week that is convenient for the potential participant. In addition to screening patients referred to the study through SBIRT, site staff used medical records to identify potentially eligible patients. Patients who have not recently attended the clinic and have no HLQ assessment record in their EHR in the previous 3 months were contacted by study staff and screened for eligibility.

Patients—referred to as “relatives” by local staff, which underscores their shared heritage—receiving care at OHC complete routine depression screening as part of most health care encounters. Individuals who report moderate levels of depression or mild, moderate, or severe risk for suicide were referred to behavioral health. The behavioral health provider could offer treatment or referral for services. The relative was informed about the present study. If they were eligible and interested, their contact information was shared with research staff, who are not OHC employees. Study staff follow up with OHC referrals and invite relatives (patients) to participate in the study. Study staff scheduled a time to complete informed consent and the baseline interview.

While the text message intervention contacted participants in the treatment group, responses were unnecessary unless scheduled, requested, or activated by an immediate crisis. However, participants frequently respond to the scheduled messages, usually expressing gratitude or mild distress. To maintain contact and maximize retention, participants in the control group and the treatment group were contacted by the study team at 6 months postbaseline assessment to confirm their contact information. Ten months after enrollment, site staff were permitted to begin contacting participants to schedule or confirm the 12-month follow-up assessment. Participants received text messages (email or private messaging for those who can no longer use text messaging) asking them to confirm the follow-up assessment appointment. If site staff do not receive a response, they contact the alternate contact provided by all participants at the baseline assessment to try and ascertain updated contact information. If a participant does not respond to the reminders and misses their scheduled appointment, the site staff will continue to try and contact them for up to 6 months after their due date, unless they decline further contact. Eighteen months after enrollment, participants were considered lost to follow-up.

If a participant became ineligible during the study (eg, incarcerated), they were withdrawn, and all study procedures were halted. Withdrawn participants who subsequently become eligible and wish to rejoin the study were required to contact site staff and then be reconsented to be re-enrolled. If a withdrawn participant was incarcerated, the study coordinator made 3 attempts to contact them upon learning of their potential release from the participant or an emergency contact. Upon being re-enrolled, a participant restarted the study procedures. At the time that enrollment concluded, only 1 individual was lost to follow-up and subsequently requested to re-enroll in the study.

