#### Primary Outcomes

Our primary outcome of interest was suicidal behavior. While suicidal ideation is more common than suicide attempts or attempts requiring hospitalization, ideation is not necessarily a concrete event and can be more difficult to measure. For this reason, ideation, attempts, and suicide-related hospitalization were all selected to measure the same underlying risk construct. The Suicidal Ideation Questionnaire-Junior, which has been validated with AIAN individuals, measured the study’s primary outcome of suicidal ideation [22]. It consists of 15 items that evaluate thoughts of death, desire to be dead, and specific thoughts of self-harm. Scores range from 0 to 90, with scores above 32 indicating active suicidal ideation [23]. The “junior” version of the questionnaire was used to accommodate participants with lower reading levels.

The SASI count (lifetime and recent) assessed the primary outcome of suicide attempts [24]. It is a concise questionnaire that determines the first, most recent, and most severe suicide attempt or nonsuicidal self-injury. It assessed the date, method used, and intent to die (ie, clear intent to die, ambivalent intent, or no intent to die), the highest level of medical treatment received (ie, none, doctor or clinic visit, emergency room, or admission to a medical unit), and lethality of each event. The SASI also posed questions about the number of attempts for each of the 17 methods, specifying intent to die, medical treatment received, and lethality for each one. Intent to die and lethality were derived from the SASI interview [24]. A lifetime version of the instrument administered at the baseline assessment captured all historical suicide attempts or nonsuicidal self-injury. A recent version of the instrument assessed only those events that occurred in the past year, both at baseline and follow-up assessments. The adapted version of the SASI used in this study simplified the language, included methods commonly used in AIAN communities, and added an assessment of drug and alcohol use at the time of the self-injury. The SASI was administered via interview.

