#### Missing Data

Our primary analysis will rely on complete case analysis. We will conduct sensitivity analyses with multiple imputation methods. Multiple imputation through chained equations will be applied when data are missing at random. We will also conduct sensitivity analyses to exclude individuals who were randomized to receive the intervention but did not receive it per the schedule outlined in Table 2 due to technological errors or temporary lapses in access to cell phone service. These additional sensitivity analyses will improve confidence in our findings.

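### The attempt outcome rests on a follow-up interview and has no fatal component, so under complete-case analysis a participant who dies by suicide leaves the attempt comparison

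*Protocol article*

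**What the plan says.** **Outcome components.** The Abstract (Methods) states: "The primary outcomes of interest are suicide-related behaviors—suicidal ideation, suicide planning, suicide attempt, or thoughts and actions requiring hospitalization". The Primary Outcomes section says "ideation, attempts, and suicide-related hospitalization were all selected to measure the same underlying risk construct". Table 2 gives the same three domains, each with its own instrument. The Objective describes the aim as effectiveness "in reducing self-reported suicide ideation, attempts, and hospitalizations". None of these places names death by suicide, and the article does not mention the death of a participant.

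**Source of the attempt outcome.** Table 2 assigns attempts to the recent SASI count. Primary Outcomes adds "The SASI was administered via interview" and "A recent version of the instrument assessed only those events that occurred in the past year, both at baseline and follow-up assessments". Ideation (SIQ-Junior) and hospitalization (Youth Health Services Measure) come from questionnaires the participant completes.

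**Participants who are not reached.** Under Recruitment and Retention, staff approach the alternate contact for new contact details, keep trying for six months past the due date, and then: "Eighteen months after enrollment, participants were considered lost to follow-up". The following paragraph describes withdrawal as a separate status.

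**Analysis.** The Analysis plan calls the primary analyses intention-to-treat. Missing Data says "Our primary analysis will rely on complete case analysis", with multiple imputation by chained equations as a sensitivity analysis where data are missing at random.

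**Other data.** Under Treatment as Usual, the type and frequency of clinic visits are extracted from the EHR after study completion. The EHR is not named as a source for any primary outcome.

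**The concern.** The trial enrols people at mild to severe risk of suicide and gives rising suicide rates as its reason. A death by suicide during the 12 months is therefore foreseeable, even if rare. Three stated rules combine badly. The attempt outcome exists only if the participant gives an interview. The outcome has no fatal component. The primary analysis keeps only participants with data. The most severe form of the target behavior is the one that cannot enter the comparison.

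This differs from ordinary dropout, where the outcome is unknown. Here it may be known, and it is what removes the person. If deaths were unequal between arms, the arm with more deaths would look better on attempts than it should. The planned comparison has about 23 events in all, so a few exclusions on one side can move the estimate.

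**Working it through.** **1. Following the rules through.** Take a randomized participant who dies by suicide in month 8.
- Attempt outcome: needs a SASI interview at follow-up. None exists.
- Other primary outcomes: need the participant's own questionnaire answers. None exist.
- Fatal event: in no outcome list, so nothing else scores the person.
- Primary analysis: complete case, so the person is absent from numerator and denominator of the attempt comparison. This holds whether the file says lost, withdrawn or died.
- Intention-to-treat governs the arm in which people are analyzed. It does not bring back someone whom the complete-case rule removes.
- Multiple imputation under missing at random draws an attempt status from models fitted to respondents. Without strongly predictive covariates, the chance of drawing an event is near the arm's own rate: 5/120 = 4.2% or 18/120 = 15% at the planned counts. Most imputed data sets would record no attempt.

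**2. The plan's own figures (Power and Sample Size).** 120 per group, 15% attempts under treatment as usual, risk ratio 0.25, 80% power. Two-sided alpha of 0.05 is assumed from the 95% CIs.
- p1 = 0.15, p2 = 0.15 × 0.25 = 0.0375, d = 0.1125, mean = 0.09375.
- n = [1.960 × √(2 × 0.09375 × 0.90625) + 0.842 × √(0.15 × 0.85 + 0.0375 × 0.9625)]² / 0.1125² = 104.2, so 105 per arm without continuity correction.
- With correction: (104.2/4) × [1 + √(1 + 4/(104.2 × 0.1125))]² = 121.3, so 122 per arm, within 3% of 120. The stated sample size is reproduced.
- Expected events: 120 × 0.15 = 18 and 120 × 0.0375 = 4.5, taken as 5.

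**3. Effect of counting deaths.** Each death adds one to the events and one to the denominator of its arm. RR = (intervention events/n) ÷ (treatment-as-usual events/n). Uncorrected chi-square = N(ad − bc)² / (product of the four margins); the corrected version replaces |ad − bc| by |ad − bc| − N/2.

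| Deaths counted | Intervention | Treatment as usual | RR | p, uncorrected | p, corrected |
|---|---|---|---|---|---|
| None | 5/120 | 18/120 | 0.28 | 0.004 | 0.009 |
| 1 intervention | 6/121 | 18/120 | 0.33 | 0.009 | 0.017 |
| 2 intervention | 7/122 | 18/120 | 0.38 | 0.018 | 0.031 |
| 3 intervention | 8/123 | 18/120 | 0.43 | 0.032 | 0.053 |
| 1 treatment as usual | 5/120 | 19/121 | 0.27 | 0.003 | 0.006 |
| 3 treatment as usual | 5/120 | 21/123 | 0.24 | 0.001 | 0.002 |

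Example, two intervention deaths: ad − bc = 7 × 102 − 115 × 18 = −1356; 242 × 1356² / (122 × 120 × 25 × 217) = 5.60, p = 0.018.

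**4. How many deaths?** The article gives no rate. Zero to three is a range chosen for illustration. An assumed 0.2% to 1% per year would give 350 × 0.002 = 0.7 to 350 × 0.01 = 3.5 deaths over both arms, but nothing in the document supports those rates.

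**The case against.** **The article is silent on deaths; it does not state a wrong rule for them.** A reader might infer that a known suicide is coded as lost to follow-up. The text does not say so: the 18-month sentence closes a passage about people who do not respond, and withdrawal shows that other statuses exist. Nor does the article say that contact details are all the alternate contact is asked for. This objection stands, but the point does not depend on the label. Exclusion follows from the interview-based outcome and the complete-case rule, both of which the article fixes.

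**Much of this belongs in the full protocol.** Coding of deaths, and reporting them to the monitoring board, are commonly left there, so no criticism is made on that score. A reader might also infer that the board would see a suicide as a mere retention loss. That is conjecture: Data and Safety Monitoring describes adverse-event entry, automatic alerts and board oversight, although it names only assessments and care texts as sources.

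**The death is excluded, not scored as a non-event.** Correct. The bias comes from omission.

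**One death would not overturn the result.** A reversal can be constructed: 5/120 versus 14/120 has uncorrected p = 0.031, and one intervention-arm death makes it 0.059. But that split is not the planned one, and before any death is added the corrected p is 0.056 and Fisher's exact p is 0.053. The example supports no general claim.

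**The outcome matches the stated aim.** The Objective speaks of self-reported outcomes, so there is no internal contradiction. That is fair, and it makes this an improvement to the definition, not an error in it.

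**Conclusion.** The concern holds as a weakness in the outcome definition. As written, a participant who dies by suicide before follow-up is left out of the attempt comparison, and neither intention-to-treat nor imputation under missing at random restores that person correctly. Severity: should-fix.

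The size is unknown. With no deaths the effect is nil. At the planned counts, one to three intervention-arm deaths move the risk ratio from 0.28 to between 0.33 and 0.43, and one to three treatment-as-usual deaths move it to between 0.27 and 0.24. Two intervention-arm deaths leave the result below 0.05 with or without continuity correction; at three, it depends on the correction. These figures assume that survivors' attempt rates equal the planned rates and that all deaths fall in one arm. Equal numbers of deaths in the two arms would still pull the ratio toward 1.

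**What to change.** Define the attempt outcome as *suicide attempt, fatal or non-fatal, within 12 months of randomization*. State that a known death by suicide in that window counts as an event for any randomized participant, whether or not a SASI was completed, and that this overrides the complete-case rule for that person.

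Before classing anyone as lost to follow-up, check vital status through the alternate-contact call and the EHR extraction already in place, in the same way in both arms.

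The cost is one sentence in the outcome definition, one question in an existing call and one item in an existing record review. The article reports recruitment and follow-up finished in New Mexico and enrollment continuing in South Dakota, so the check can be built in at one site and made retrospectively at the other. The change should be recorded before outcomes are examined by arm. The downside is that cause of death will sometimes be uncertain; a sensitivity count with such deaths included and then excluded covers this.
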